#### Tertiary objective

To determine the cost-effectiveness of empagliflozin compared with NPH insulin in treating GIDM. Outcome measure: Health economic analyses will estimate the cost of health care expenses in the two treatment arms. Incremental cost–effectiveness ratio (ICER) analysis will be conducted [27]. ICER analysis compares the incremental costs associated with one intervention (empagliflozin) over another (NPH insulin) with the incremental outcome costs (negative or positive) of one intervention over another. In this study the outcome includes but not limited to costs of: Investigational products, blood glucose monitoring, expenses for hospitalization.

#### Safety objectives

To evaluate the safety and tolerability of empagliflozin compared with NPH insulin in treating GIDM. Outcome measures: SAEs. Discontinuation of investigational product (IP) due to adverse events. Changes in clinical chemistry/hematology parameters including finger prick ketones. AEs of interest (urogenital infections, volume depletion, diabetic ketoacidosis (DKA), HHS, hypoglycemic events and other AEs needing any treatment. Number of contacts between patient and general practitioner due to diabetes-related problems, and any admissions to hospital.

Percentage in each group that needing rescue medication due to hyperglycaemia. Outcome measure: Interviews and SP. Dose of sliding scale needed.

### Statistics

#### Power

A total of 74 patients should be included to allow randomization of approximately 37 patients in each arm, and for at least 29 patients to complete 30 days of treatment per arm, with alpha set to 0.05 and beta 0.90. It is estimated that a total of 58 completing patients can provide 90% power to detect a significant difference (two-tailed p-value ≤0.05) between the two treatments in reduction of plasma glucose, if there is a true difference of 2 mmol/L (non-inferiority limit) with a standard deviation (SD) for plasma glucose of 2.6 mmol/L. In our own recent study, which included 1131 blood glucose measurements in patients with newly diagnosed GIDM, we found an SD of 4.2 mmol/L [13]. In another study with 21 patients that developed GIDM after prednisolone, an SD of 1 mmol/L was calculated [28]. Thus, because the true SD for glucose for GIDM is not known, the SD used for the power calculation was pragmatically calculated as a mean from the 2 studies.

It is expected that up to 16 patients (25%) may leave the study prematurely, thus a total minimum of 74 patients will be included and at least 58 complete the study.

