#### Data presentation

Numeric data will be shown as mean or medians with inter-quartile ranges (IQR) or ranges where relevant. Frequencies will be shown as numbers with percentages and 95% confidence intervals (CI) where relevant. All statistical tests will be 2-tailed and *p* < .05 considered statistically significant. Any missing data will be presented in the appendix of the main manuscript.

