#### Primary analysis

A comparison between groups of differences in mean daily plasma glucose from 14-day CGM using a T-test with a 95% confidence interval. If we, based on the primary analysis, can be 95% sure that the biggest difference in glucose is not more than 2 mmol/L then non-inferiority for the experimental arm (empagliflozin) is concluded.

Subgroup analysis will be done with ANOVA, which will include stratification on dose of glucocorticoids and more.

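### The 90% power claimed for 58 completers belongs to a one-sided 5% test; under the plan's own two-tailed 5% / 95% CI rule it is about 82%

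*Protocol article*

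**What the plan says.** The Power section sets the error rates "with alpha set to 0.05 and beta 0.90" and claims that "a total of 58 completing patients can provide 90% power to detect a significant difference (two-tailed p-value ≤0.05) between the two treatments", with 29 of the 58 in each arm. The assumed true difference is 2 mmol/L, which the same sentence labels the non-inferiority limit, and the SD is 2.6 mmol/L. That SD is the mean of 4.2 and 1 from two studies. The plan is to randomise 74 patients, about 37 per arm, and to allow for up to 16 losses.

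The Data presentation section adds: "All statistical tests will be 2-tailed", with significance at the 5% level. The Primary analysis section compares mean CGM glucose between arms "using a T-test with a 95% confidence interval". It concludes non-inferiority if the investigators "can be 95% sure that the biggest difference in glucose is not more than 2 mmol/L".

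No section states a one-sided 5% test or a 90% confidence interval.

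**The concern.** A sample size, a significance level and a power must belong to the same test. Here the sample size is the one-sided 5% answer, while the text and the analysis are two-sided 5%. If so, the chance of missing true non-inferiority at 58 completers is nearly double the one implied.

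The hypothesis is also framed the wrong way round. The article describes a non-inferiority trial but gives power to detect a difference when the true difference equals the margin. If empagliflozin really were 2 mmol/L higher, concluding non-inferiority would be an error, and the 95% CI rule makes that happen 2.5% of the time. The true difference under which non-inferiority is to be shown is not stated.

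Finally, the 95% assurance in the decision rule, read without the sentence before it, could mean a one-sided 95% bound. That is the only reading that fits the sample size, so the inconsistency touches the primary decision rule as well as the power.

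**Working it through.** **Inputs.** From the Power section: SD σ = 2.6 mmol/L; difference or margin Δ = 2 mmol/L; n = 29 completers per arm; target power 90%; two-tailed 5%. From Study design: 1:1 allocation. Assumption, not in the article: true difference 0 for the non-inferiority reading. The distance to be resolved is then 2 − 0 = 2 mmol/L, the same as in the literal superiority wording, so both readings give essentially the same power and sample size.

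**1. Reproducing the plan's figure.** Normal approximation:

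n per arm = 2 (z_α + z_β)² (σ/Δ)², with (2.6/2)² = 1.69 and z_β = 1.2816 for 90% power.

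- One-sided 5% (z_α = 1.6449): 2 × (2.9264)² × 1.69 = 28.95, so 29 per arm and 58 in total. This is the article's number.
- Two-sided 5% (z_α = 1.9600): 2 × (3.2415)² × 1.69 = 35.5, so 36 per arm and 72 in total.

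With the planned t-test, the two-sided requirement is 36.50, so 37 per arm and 74 in total.

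**2. Power at 29 per arm.** Standard error = 2.6 × √(2/29) = 0.683. Distance in standard errors = 2/0.683 = 2.929.

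| Test | Normal approximation | Noncentral t, 56 df |
|---|---|---|
| One-sided 5% | Φ(2.929 − 1.645) = 90.0% | 89.4% |
| Two-sided 5%, or upper limit of 95% CI (one-sided 2.5%) | Φ(2.929 − 1.960) = 83.4% | 82.1% |

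On the t-test the type II error is 100 − 82.1 = 17.9%, against the intended 10%.

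**3. What the two readings of the decision rule would require.** The t critical values with 56 df are 2.003 (one-sided 2.5%) and 1.673 (one-sided 5%). With a standard error of 0.683, the observed difference would have to lie below:

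- 95% CI: 2 − 2.003 × 0.683 = 0.63 mmol/L;
- one-sided 95% bound: 2 − 1.673 × 0.683 = 0.86 mmol/L.

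An observed difference between about 0.63 and 0.86 mmol/L would pass one rule and fail the other.

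**4. Sensitivity (two-sided 5%, noncentral t).**

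- 25 per arm, the minimum of 50 evaluable patients given under Study design and Withdrawal from study: 76.0%.
- 33 per arm: 86.8%.
- 37 per arm, everyone randomised: 90.4%.
- 29 per arm if empagliflozin is truly 0.5 mmol/L higher (an illustrative assumption, not a figure from the article), so the distance is 1.5: 57.9%.

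**The case against.** The best counter-argument concerns who will be analysed. The 58 are patients who complete 30 days of treatment, whereas the primary endpoint uses CGM from the first 14 days and requires 70% of those data. The Statistical analysis plan section also foresees an intention-to-treat analysis of all randomised subjects. Some patients who leave after day 14 could still contribute, so the analysed number may exceed 58. With all 74, power would be 90.4%. This stands as a limit on the consequence: 82% is the power at 58 analysed patients, not a forecast for the trial. It does not rescue the sentence, which attaches 90% to 58 completers, and the CGM data requirement may keep the analysed number below 74.

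The mis-framed hypothesis has no numerical effect, since both readings give the same result, and the stated beta is plainly a slip for power. Both are fair points; these remain errors of wording. It is also fair that the confidence interval and the 2-tailed rule indicate which decision rule is meant. They are the reason the calculation above uses one-sided 2.5%.

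Lastly, the error does not affect the type I error of the 95% CI rule or the estimate, and the gap is small beside the uncertainty in the SD. At 29 per arm, two-sided power is 43% with the SD of 4.2 and close to 100% with the SD of 1, the two values that the article averages. That is true, but it does not make the stated figure correct.

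**Conclusion.** The concern holds. For the test the article specifies, 58 completers give 82.1% power (t-test) or 83.4% (normal approximation), not 90%. The shortfall is 7 to 8 percentage points, and the type II error is about 18% instead of 10%. The published sample size matches only a one-sided 5% test, which the Power, Data presentation and Primary analysis sections all contradict. For 90% power under the stated rule, 72 (normal) or 74 (t-test) evaluable patients are needed in total.

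This rests on the article's SD of 2.6, its margin of 2 mmol/L, equal arms, a true difference of 0 and exactly 29 analysed per arm. More analysed patients would raise the power; a true difference unfavourable to empagliflozin would lower it.

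**What to change.** Rewrite the power statement and the decision rule so that they describe one test. Suggested text for the Power section:

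> Non-inferiority is concluded if the upper limit of the two-sided 95% confidence interval for the difference in mean CGM glucose (empagliflozin minus NPH insulin) is below 2 mmol/L, corresponding to a one-sided alpha of 0.025. With 29 evaluable patients per arm, an SD of 2.6 mmol/L and a true difference of 0, power is 82%.

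Use the same rule in the Primary analysis section in place of the 95% assurance wording. Replace the stated beta of 0.90 with a beta of 0.18 to match. It would help to give the power for all 74 randomised (90%) next to the figure for 58, so the reader sees the range. Do not restore the 90% by moving to a one-sided 5% bound, which would relax the stated rule.

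This costs only wording, and a less favourable power figure.

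If the sponsor wants to keep 90% power, the alternative is a target of 37 evaluable patients per arm, 74 in total. Allowing for losses, that means randomising 74/(1 − 16/74) = 94.4, so 95 patients at the loss rate implied by 16 of 74, or 74/0.75 = 98.7, so 99 patients at the stated 25%.

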### Withdrawal from study

If a patient discontinues the IP, the patient will be replaced by further recruitment to maintain the required total minimum of 50 evaluable patients. Discontinuation of IP due to normoglycaemia after treatment with glucocorticoids are stopped within the 30-day treatment period will not be withdrawals and the visits will continue as planned.

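### The replacement rule protects a minimum of 50 evaluable patients while the power statement needs 58 completers; the two minimums must be reconciled, and the 25% attrition label corrected

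*Protocol article*

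**What the plan says.** Study design and Withdrawal from study carry the same rule: a patient who discontinues the investigational product is replaced by further recruitment "to maintain the required total minimum of 50 evaluable patients". Stopping because glucose has normalised after the glucocorticoid ended does not count as a withdrawal.

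The Power section uses other numbers. It plans 74 inclusions, about 37 per arm, so as to have "at least 29 patients to complete 30 days of treatment per arm". It states that 58 completers give "90% power to detect a significant difference (two-tailed p-value ≤0.05) between the two treatments", with an SD of 2.6 mmol/L and "if there is a true difference of 2 mmol/L (non-inferiority limit"). On attrition it says: "It is expected that up to 16 patients (25%) may leave the study prematurely, thus a total minimum of 74 patients will be included", and it adds that at least 58 are to complete.

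Three other statements matter for the check. Data presentation says "All statistical tests will be 2-tailed". Primary analysis compares the arms "using a T-test with a 95% confidence interval" and sets the result against 2 mmol/L. The primary objective, under Definition of endpoints, admits a patient to the analysis if 70% of the possible CGM data over 14 days are available.

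**The concern.** The only rule on replacing lost patients protects 50, while the power claim depends on 58. No section explains the difference or says that the two figures count different things. The units also differ. The replacement rule counts evaluable patients without defining the term, the Power section counts patients who complete 30 days of treatment, and the primary endpoint needs only sufficient CGM data from the first 14 days. Staff who decide whether a loss must be replaced could follow either figure and believe they are following the protocol.

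The attrition sentence raises a smaller doubt of the same kind, because its count and its percentage do not fit any base that the document uses.

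What is at stake is the precision of a non-inferiority comparison in a small trial, and whether the published design figures can be relied on.

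**Working it through.** **Inputs (Power section unless noted).** Margin 2 mmol/L; SD 2.6 mmol/L; two-tailed 0.05; 1:1 allocation; 58 completers (29 per arm); 74 included; 16 lost, labelled 25%. The section prints "with alpha set to 0.05 and beta 0.90"; since it claims 90% power, 0.90 is read as the power. The floor of 50 comes from Study design and Withdrawal from study. A true difference of 0 is assumed, as is usual for non-inferiority. The two-sided 95% interval in Primary analysis corresponds to one-sided 0.025.

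**Step 1: reproduce 58.** The normal approximation is n per arm = 2 × [SD × (z_alpha + z_power) / margin]².
- Two-sided 0.05: 2 × [2.6 × (1.960 + 1.282) / 2]² = 35.5, so 36 per arm (72). The exact noncentral t needs 37 per arm (74).
- One-sided 0.05: 2 × [2.6 × (1.645 + 1.282) / 2]² = 28.9, so 29 per arm (58).

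The printed 58 does not follow from the stated two-tailed test. It does follow from a one-sided 0.05.

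**Step 2: power at each minimum.** Noncentral t with 2n − 2 degrees of freedom and noncentrality 2 / [2.6 × √(2/n)], which is 2.72 for n = 25 and 2.93 for n = 29 per arm.

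| Evaluable | Two-sided 0.05 | One-sided 0.05 |
|---|---|---|
| 50 (25 + 25) | 76.0% | 85.0% |
| 58 (29 + 29) | 82.1% | 89.4% |
| 74 (37 + 37) | 90.4% | 94.9% |

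The normal approximation gives 77.6% and 83.4% two-sided, and 85.9% and 90.0% one-sided, at 50 and 58.

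**Step 3: split the shortfall at two-sided 0.05.**
- From 90% to 82.1%: about 8 points, because 58 is too few for the stated test. This is present whichever minimum applies.
- From 82.1% to 76.0%: about 6 points, due to 50 versus 58. At one-sided 0.05 this part is 89.4 − 85.0 = about 4 points.

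**Step 4: attrition.**
- 16/74 = 21.6%; 16/58 = 27.6%; 16/0.25 = 64, a number the document does not use.
- The counts agree: 74 − 16 = 58.
- A true 25% loss from 74 leaves 74 × 0.75 = 55.5, so about 55 (28 + 27: power 80.0% two-sided).
- Keeping 58 at a true 25% loss needs 58/0.75 = 77.3, so 78 included.
- A likely origin of the label is 29 × 1.25 = 36.25, rounded up to 37 per arm, which is 74. That adds 25% to the completers instead of dividing by 0.75.

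**The case against.** The tempting stronger reading is that recruitment may end at 50 evaluable patients, so that the trial runs at 76% power against a claimed 90%. The document does not support this. The sentence about 50 is a replacement rule with a minimum; it sets no stopping point. The Power section separately requires 74 included and 58 completing, and a trial that meets 58 also meets 50. Ending at 50 would mean disregarding the Power section. The 14-point gap also merges two errors, and the larger part would remain if every section said 58.

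A second tempting reading is that the trial must miss 58 because of its own 25%. That prefers the percentage to the stated count of up to 16, which leads exactly to 58. Completing 30 days is also a later milestone than having usable CGM data from the first 14 days, so some patients who leave between day 14 and day 30 can still enter the primary analysis. Counting 55 completers as only 55 evaluable would therefore be pessimistic.

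It can also be said that 50 and 58 count different things. The document does not say so. Usable 14-day data come earlier than 30-day completion, which gives no reason for a lower required number.

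All of this limits the consequence. The contradiction itself stands: two required minimums, in sections that do not refer to each other.

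**Conclusion.** The conflict between 50 and 58 is real and should be fixed. Its own cost is about 6 points of power at the stated two-sided 0.05, or about 4 points at one-sided 0.05. These figures assume SD 2.6, margin 2, a true difference of 0, equal arms and a t-test. They describe what the lower minimum would cost if it were followed, and not a forecast that it will be.

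The remaining gap to 90% is a separate error that any correction here must not leave in place: under the stated two-tailed test, 90% needs 74 evaluable patients, which is the whole planned inclusion with no losses. The 25% label is a minor error, since the counts agree with each other.

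**What to change.** 1. In Study design and in Withdrawal from study, replace the minimum of 50 evaluable patients with 58, so that one number is used throughout.
2. Define evaluable by the criterion already given under the primary objective, 70% of possible CGM data over the first 14 days, and use the same unit in the Power section.
3. Restate attrition as 16 of 74, or 22%. If a 25% loss is really expected, either state about 55 remaining or plan 78 inclusions.
4. Restate the power at 58 as about 82% at two-sided 0.05. A figure of about 89-90% can stand only if a one-sided 0.05 is declared, and then Data presentation and Primary analysis must agree with it. Harmonising on 58 without this step would leave the larger error in print.

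The cost is wording and a less favourable stated power. The planned inclusion of 74 need not change unless the sponsor keeps both 58 and a 25% loss, or insists on 90% at two-sided 0.05.

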### Statistical analysis plan

Before the randomization code will be added to the cleaned dataset, a thorough plan for statistical analysis will be elaborated and accepted by the statistician and investigators. Intention-to-treat (all randomized subjects) and per-protocol statistical analysis will be conducted by the investigators (responsible: [name]), in collaboration with a statistician. All data will be described including data-incompleteness as well as reasons for data-incompleteness. Data will be analyzed blinded by the daily coordinator of the study [name] in collaboration with the principal investigator [name]. Any changes to the statistical analysis plan will be described in any future publications.

#### Data presentation

Numeric data will be shown as mean or medians with inter-quartile ranges (IQR) or ranges where relevant. Frequencies will be shown as numbers with percentages and 95% confidence intervals (CI) where relevant. All statistical tests will be 2-tailed and *p* < .05 considered statistically significant. Any missing data will be presented in the appendix of the main manuscript.

#### Primary analysis

A comparison between groups of differences in mean daily plasma glucose from 14-day CGM using a T-test with a 95% confidence interval. If we, based on the primary analysis, can be 95% sure that the biggest difference in glucose is not more than 2 mmol/L then non-inferiority for the experimental arm (empagliflozin) is concluded.

Subgroup analysis will be done with ANOVA, which will include stratification on dose of glucocorticoids and more.

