## Background

Glucocorticoid treatment is frequent in inpatients and outpatients in medical specialties as rheumatology, oncology, haematology, neurology, nephrology, and pulmonology. A well-known metabolic side effect from treatment with glucocorticoid is hyperglycaemia and diabetes (and worsening of pre-existing diabetes). The acute symptoms of diabetes include general discomfort, polyuria, thirst, and blurry vision. Moreover, high plasma glucose during hospitalisation is associated with increased risk of inflammation, infection [1] and mortality [2, 3] and glucocorticoid induced diabetes (GIDM) is associated with increased mortality [4].

The diabetic effect of glucocorticoids relies partly on induction of insulin resistance in the liver, skeletal muscles and adipose tissue. In addition, glucocorticoids may reduce beta-cell function, reduce the insulinotropic effects of incretin hormones and increase glucagon levels. In concert, these changes lead to increased plasma glucose concentration [5].

The prevalence of GIDM depends on the population studied and the duration and dose of glucocorticoid. In a review from 2018 including 13 very heterogeneous studies, the overall incidence of GIDM was 18.6% [6]. The glucocorticoids were administered in different regimens, on different indications, and for both malignant and non-malignant diseases.

Guidelines on detection and management of hyperglycaemia in hospitalized patients (in the non-critical care setting) recommend initiation of sliding scale insulin (aspart) therapy or other insulin regimens in case of hyperglycaemia during glucocorticoid treatment [7, 8]. The evidence for the superiority of this treatment is however poor and it is a clinical experience that insulin treatment during admission to hospital is associated with episodes of both hypo- and hyperglycaemia. Insulin is considered a high-risk treatment, classified from the Danish authorities’ stratification [9].

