### Rationale for study design and endpoints

GIDM is different from other types of diabetes because the primary feature is postprandial hyperglycaemia and fasting blood glucose can often be normal. Often the hyperglycaemia starts within the first 1–3 days of glucocorticoid treatment – thus with a 30-day trial period, HbA_1c_ will be unreliable as an endpoint, as HbA_1c_ reflects the average blood glucose during the last 8–12 weeks. Fasting glucose level will also be unreliable, as glucocorticoids are mostly given in the morning and thus the effect on plasma glucose usually begin before dinner [13] and diminish during night. Thus, the primary outcome measure is the difference between treatment arms in mean glucose from CGM in the first 14 days of treatment. Patients will wear a blinded CGM system on day 0–14. CGM systems provide subcutaneously glucose values every 5 min, which via algorithms is “translated” into plasma glucose values. These data provide us with a unique possibility to gain knowledge about the glucose fluctuations during day and night in patients with GIDM in the two treatment arms. No previous trials have gathered blinded CGM data on patients with GIDM. In addition, the CGM data can form the basis of a mathematical model which make it possible - at least to some extent - to predict glucose values throughout the day and night in this patient population. This could be helpful for patients and healthcare professionals when planning treatment and blood glucose measurements.

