### Data collection and randomization procedure

A web based electronic CRF (REDcap®) is provided and all data related to the trial will be recorded in here and provide the basis for a central database. Randomization (1:1) in REDcap® is stratified by dose of glucocorticoid at the day of the screening visit in blocks of 2,4 and 6. The patient will belong to one of two groups: Group 1: Glucocorticoid dose equivalent to 20–75 mg prednisolone per day. Group 2: Glucocorticoid dose equivalent to more than 75 mg prednisolone per day. No further stratification will be done to ensure a ‘real life’ study.

Randomization in REDcap® was set up by independent personnel not involved in other parts of the trial.

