### Visit procedures

Patients are seen in the hospital setting at 5 University Hospitals in Copenhagen, Denmark for visit 0–7 see Fig. 2 and Table 1. If not hospitalized, patients will be seen at the out-patient clinics at the abovementioned locations. Prior to any protocol-related procedures written informed consent is obtained. The patient is screened for in- and exclusion criteria at visit 0 and information about demography, medical and surgical history, family history of type 1 and 2 diabetes mellitus, current medication, indication for glucocorticoid treatment and dose of glucocorticoid, date of diagnosis of GIDM, vital signs: weight, height, blood pressure, pulse, general physical examination, volume status (lung auscultation and peripheral oedema examination (pitting) and weight), laboratory tests: Haemoglobin, fructosamine, HbA_1c_, plasma glucose, C-peptide, leukocytes with differential count, CRP, platelet count, iron, transferrin, MCV, reticulocytes, albumin, ALAT, ASAT, alkaline phosphatase, LDH, bilirubin, calcium-ion, lipids, creatinine, potassium, sodium, urea. Finger prick ketones, genetic research material collection for future biobank (plasma, serum, whole blood), pregnancy test in women of child-bearing potential with a standard dip-stick and urine test (signs of urinary tract infection).

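### The primary t-test leaves out the randomisation stratum and baseline glucose; adjusting for both is a low-cost gain in precision whose size the documents do not fix

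*Protocol article*

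**What the plan says.** Under Primary analysis the comparison is "A comparison between groups of differences in mean daily plasma glucose from 14-day CGM using a T-test with a 95% confidence interval", with non-inferiority concluded if the interval excludes a difference above 2 mmol/L. No covariate is named. Dose appears in the next paragraph only: "Subgroup analysis will be done with ANOVA, which will include stratification on dose of glucocorticoids and more".

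Under Data collection and randomization procedure, allocation is "stratified by dose of glucocorticoid at the day of the screening visit in blocks of 2,4 and 6". The two strata are 20–75 mg and more than 75 mg prednisolone equivalent per day, and dose is the only stratifier.

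Under Visit procedures, the visit 0 assessments include "laboratory tests: Haemoglobin, fructosamine, HbA_1c_, plasma glucose, C-peptide". There is no pre-treatment sensor baseline: "Patients will wear a blinded CGM system on day 0–14".

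Secondary analysis prescribes a t-test for continuous outcomes as well. The Statistical analysis plan section says a fuller plan will be agreed before the randomisation code joins the cleaned data. Nothing in the article indicates that this plan will adjust the primary comparison.

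**The concern.** Stratified blocks make the arms nearly equal in dose mix, so differences between dose strata contribute almost nothing to the true sampling variance of the arm difference. The two-sample t-test does not know this. Its pooled SD still contains the between-stratum variance, so the standard error is too large whenever dose predicts glucose. Visit 0 glucose works differently. Leaving it out does not bias the standard error, but outcome variance that could have been explained stays in the residual, and any chance imbalance between two arms of about 29 is left uncorrected.

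At stake is the width of the interval set against the 2 mmol/L margin. In a non-inferiority trial of this size, an interval wider than necessary can leave a true non-inferiority result inconclusive.

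**Working it through.** **Inputs from the Power section.** Margin 2 mmol/L, SD 2.6 mmol/L, 58 completers (29 per arm), two-tailed 0.05, 90% power. True difference is taken as 0. The share of outcome variance explained by the covariates (R²) is not in the documents and is varied.

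**The plan's own figure.** n per arm = 2 × [SD × (z₁₋α + z₀.₉₀) / margin]².
- One-sided 0.05: 2 × [2.6 × (1.645 + 1.282) / 2]² = 28.95, so 29 per arm and 58 in total, which matches the plan.
- Two-sided 0.05: 2 × [2.6 × (1.960 + 1.282) / 2]² = 35.5, so 36 per arm and 72 in total.

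Under the 95% interval that the plan uses, 29 per arm gives 83.4% power by the normal formula and 82.1% by the noncentral t. That shortfall is a separate sample-size matter. It matters here only because it sets the starting point at about 82%.

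**Power after adjustment.** Residual SD = 2.6 × √(1 − R²). Standard error = residual SD × √(2/29). Half-width = t₀.₉₇₅ × standard error, with 56 degrees of freedom unadjusted and 54 with two covariates. Power is from the noncentral t at one-sided 0.025.

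| R² | Residual SD | Half-width (mmol/L) | Power |
|---|---|---|---|
| 0 (t-test) | 2.60 | 1.37 | 82.1% |
| 0.05 | 2.53 | 1.33 | 83.9% |
| 0.10 | 2.47 | 1.30 | 85.8% |
| 0.20 | 2.33 | 1.22 | 89.5% |
| 0.22 | 2.30 | 1.21 | 90.3% |
| 0.30 | 2.18 | 1.15 | 93.0% |

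For baseline glucose alone, R² is the squared correlation r with the 14-day mean. By the same method, r = 0.1 / 0.2 / 0.3 gives 82–83% / 84% / 85%, and r = 0.4 / 0.5 / 0.6 gives 88% / 91% / 95%.

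**Coverage when the stratifier is ignored.** With exact balance within strata, the true variance is (1 − R²ₛ) times what the t-test assumes, where R²ₛ is the stratum's share. The effective critical value is 2.003 / √(1 − R²ₛ). For R²ₛ = 0.10 this is 2.003 / 0.949 = 2.11, a coverage of about 96%. For two equal strata separated by a gap g, R²ₛ = 0.25 × g² / 2.6². A gap of 1.0, 1.5 or 2.5 mmol/L gives 0.04, 0.08 or 0.23.

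**Simulation check** (58 patients, two strata balanced by arm, 20,000 runs each):
- Stratum 0, baseline 0: coverage 94.9% with both methods; power 82.2% unadjusted, 81.4% adjusted.
- Stratum 0.05, baseline 0.10: coverage 95.3% unadjusted, 94.8% adjusted; power 82.1% and 86.6%.
- Stratum 0.10, baseline 0.20: coverage 96.0% and 94.9%; power 83.2% and 92.5%; one-sided type I error of the t-test 2.05% against a nominal 2.5%.
- Stratum 0.20, baseline 0.20: coverage 97.1% and 95.1%; power 85.0% and 95.9%; type I error of the t-test 1.4%.

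**The case against.** **A valid test needs no repair.** The t-test after stratified randomisation has type I error at or below nominal, and for a non-inferiority claim that is the safe direction. This stands. A reader might infer that the planned test is invalid or that adjustment is needed to protect the error rate; the calculations show neither. Nor does leaving out baseline glucose cause over-coverage. Only the ignored stratifier does.

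**The loss is conditional.** A reader might also infer that the interval is too wide and power is lost as a matter of fact. The documents report no correlation, R² or stratum difference. The Background sentence "The prevalence of GIDM depends on the population studied and the duration and dose of glucocorticoid" concerns how often the condition arises, not how high glucose runs in those who have it. A stratum gap of 2.5 mmol/L would exceed the margin itself and explain 23% of the variance; a gap of 1.0–1.5 adds at most about two points of power.

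**Visit 0 glucose may predict weakly.** It is a single laboratory value. The article describes strong time-of-day variation and often normal fasting values, permits short-term insulin before screening, and restricts the entry range. Treatment doses are then changed in response to glucose, and glucocorticoids may stop during follow-up. All of this argues for looking at the low end of the range.

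**The plan is consistent with itself.** The sample size used an unadjusted SD, so nothing is lost against the design's own assumption, only against what an adjusted model could reach. This stands too.

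**It could be left to the analysis plan.** This carries some weight, since a fuller plan is promised. But the article is not silent on method. It names the test and assigns the stratifier to subgroup analysis, so the suggestion replaces a stated choice.

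**Conclusion.** The point holds as an efficiency improvement, not as an error that threatens the conclusion. The stated primary test leaves out the one factor used to stratify randomisation and a baseline measurement of the same quantity as the outcome. If dose stratum predicts glucose, the interval is conservative; if baseline glucose predicts it, precision is given up.

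At 29 per arm, SD 2.6 and a two-sided 95% interval, power runs from about 82% at R² = 0 to about 86% at 0.10, 90% at 0.20–0.22 and 93% at 0.30. At R² = 0 the simulated cost of adjusting is less than one point. These figures rest on an assumed R², a true difference of zero and the plan's SD. The range has to be read from zero upwards, because the documents do not support any particular value.

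**What to change.** Before the randomisation code is added to the cleaned dataset, specify the primary analysis as a linear model of 14-day mean sensor glucose on arm, randomisation stratum (20–75 mg, more than 75 mg) and visit 0 plasma glucose. Conclude non-inferiority if the upper limit of the two-sided 95% interval for the adjusted arm difference lies below 2 mmol/L. Keep the unadjusted t-test as a sensitivity analysis.

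For continuous secondary outcomes, adjust for the stratum. Add visit 0 glucose only where the outcome is glycaemic. For others, such as the quality-of-life rating scale, use the outcome's own baseline where it was measured.

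The cost is a sentence or two in the analysis plan and a note of the change from the published method. No new data or visits are needed. The timing matters: a covariate model chosen after the arms are known could look data-driven.
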